### 2.7. Data Collection and Analysis

Self-report questionnaires (SWLS, DASS-21, MAAS, SHS, LIS) are administered on paper at baseline (T0) and post-intervention (T2) by trained site coordinators in quiet studio environments (~20–30 min per assessment). Questionnaires are entered into a secure electronic database with double-entry verification.

Demographic and baseline characteristics are summarized using descriptive statistics (means, standard deviations, medians, frequencies, percentages). Shapiro–Wilk tests and visual inspection (Q-Q plots, histograms) assess normality for all primary outcome variables. Between-group demographic comparisons use independent-samples *t*-tests (continuous) and chi-square tests (categorical). Internal consistency is assessed using Cronbach’s alpha (α ≥ 0.70); test–retest reliability via intraclass correlation coefficients (ICC ≥ 0.70) in the control group.

If normality is met (Shapiro–Wilk *p* > 0.05), a 2 (Group) × 2 (Time) mixed-model repeated-measures ANOVA is conducted on each primary outcome, with Bonferroni-corrected α = 0.01 to control Type I error. Alternative testing via MANOVA (Wilks’ Lambda, α = 0.05) proceeds to univariate ANOVAs if significant. ANCOVA with T0 baseline covariates is conducted with Levene’s test assessing homogeneity of variance; if violated (*p* < 0.05). Effect sizes and 95% confidence intervals are reported.

If normality is violated (Shapiro–Wilk *p* < 0.05), non-parametric tests will be used: Friedman’s test (within-group time effects), Mann–Whitney U (between-group comparisons), Wilcoxon signed-rank test (within-group pre–post). Post hoc pairwise comparisons use Bonferroni-corrected alpha. Pearson correlations (Bonferroni-corrected) for normally distributed variables; Spearman’s rank-order correlations for non-normal variables. Correlations ≥ |0.30| are highlighted. Quantitative analyses use IBM SPSS v. 28; results are reported per CONSORT guidelines [31] with summary statistics, 95% confidence intervals, and effect sizes. Significance level: α = 0.05 (two-tailed) unless otherwise specified (Bonferroni-corrected α = 0.01).

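### Section 2.7 corrects Pearson but not Spearman correlations for multiplicity, so a normality check decides whether a correlation is corrected

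*Protocol article*

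**What the plan says.** All of the relevant text is in the protocol article, section 2.7 (Data Collection and Analysis).

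- The primary outcomes are analysed "with Bonferroni-corrected α = 0.01 to control Type I error".
- On the non-parametric route, "Post hoc pairwise comparisons use Bonferroni-corrected alpha". This covers pairwise comparisons and does not mention correlations.
- For correlations the plan has "Pearson correlations (Bonferroni-corrected) for normally distributed variables" and then "Spearman’s rank-order correlations for non-normal variables". Only the first carries a correction.
- "Correlations ≥ |0.30| are highlighted", whichever method produced them.
- The section closes with a general rule: "Significance level: α = 0.05 (two-tailed) unless otherwise specified (Bonferroni-corrected α = 0.01").

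The article does not list the correlations, their number, the time point, or whether they are run on the pooled sample or by arm.

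**The concern.** Multiplicity depends on how many correlations are tested and has nothing to do with the shape of their distributions. The section nevertheless ties the correction to the method, and the method to a normality check. Nothing is specified for Spearman, so the general 0.05 rule applies to each of those tests.

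Two things follow. Correlations of the same size, on the same number of participants, can be called significant on one branch and not on the other. And because the choice of method refers to variables, a single matrix may be part Pearson and part Spearman, with some cells corrected and others not, and with no clear divisor for the Pearson cells. What is at stake is chance associations between well-being scales being reported as findings.

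**Working it through.** **Inputs.** From section 2.7: five questionnaires (SWLS, DASS-21, MAAS, SHS, LIS), a general two-sided level of 0.05, and a Bonferroni level of 0.01. From Table 1: DASS-21 has three subscales. From section 2.4: 114 participants, 38 control and 76 intervention. The family of correlations is not given, so its size is an assumption here.

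**The plan's own figure.** 0.05 / 5 = 0.01. The stated level reproduces exactly and is sized for the five primary outcomes.

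**Possible families.** One score per scale at one time point gives 5 × 4 / 2 = 10 pairs. Scoring the three DASS-21 subscales separately gives seven variables and 7 × 6 / 2 = 21 pairs.

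**Family-wise error.** With m0 true null correlations, each tested at level a and treated as independent, the error is 1 − (1 − a)^m0. All pairs are assumed to go to Spearman.

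| Family | True nulls | Level per test | Family-wise error |
|---|---|---|---|
| 10 pairs | 10 | 0.05 | 1 − 0.95^10 = 40.1% |
| 10 pairs | 6 | 0.05 | 1 − 0.95^6 = 26.5% |
| 10 pairs | 4 | 0.05 | 1 − 0.95^4 = 18.5% |
| 10 pairs | 2 | 0.05 | 1 − 0.95^2 = 9.8% |
| 21 pairs | 21 | 0.05 | 1 − 0.95^21 = 65.9% |
| 10 pairs | 10 | 0.05/10 = 0.005 | 1 − 0.995^10 = 4.9% |
| 21 pairs | 21 | 0.05/21 = 0.00238 | 4.9% |
| 10 pairs | 10 | 0.01 | 1 − 0.99^10 = 9.6% |
| 21 pairs | 21 | 0.01 | 1 − 0.99^21 = 19.0% |

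The last two rows show that carrying over the primary-outcome level of 0.01 would not be enough.

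**Check by simulation.** Spearman correlations among five independent skewed variables, 6,000 runs per setting, gave at least one p < 0.05 in 39.5% of runs at n = 114, 41.0% at n = 76 and 41.1% at n = 38. At 0.005 per test the figures were 4.7%, 4.8% and 5.2%. These agree with the formula.

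**What changes in practice.** The critical value is |r| = t / √(n − 2 + t²), with t the two-sided critical value on n − 2 degrees of freedom. If all 114 are pooled, it is 0.184 at level 0.05 and 0.261 at level 0.005. A correlation of, say, 0.22 would be significant on the Spearman branch and not on the Pearson branch.

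**The 0.30 highlight.** At n = 114, t = 0.30 × √(112 / 0.91) = 3.33, so p = 0.0012. Used as a filter on ten null pairs this gives 1 − (1 − 0.0012)^10 = 1.2% (1.3% simulated), which is stricter than Bonferroni.

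**The case against.** The best reply is that this is compressed wording. The sentence is a verbless, two-part list in a journal article, and the same paragraph calls for Bonferroni correction of its post hoc comparisons, so the authors may well have meant the correction to cover both methods. That is plausible, and the text does not show a deliberate choice to leave Spearman uncorrected. But an analyst following the sentence as printed would apply the asymmetry. It is something the article states, so it is not a detail left to a fuller document.

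The second reply is that 40% is not a figure in the article. That stands. It needs ten pairs, all of them on the Spearman branch, and every true correlation equal to zero. The last condition is hard to defend for scales of life satisfaction, happiness, distress, mindfulness and leisure involvement. The figure should be read only as one point in a range.

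A reader might also infer that the 0.30 highlight is a failed error control. The article does not support this. The highlight is a reporting convention and is never presented as a multiplicity rule. On all 114 participants it is stricter than Bonferroni. It would be loose only in a small subgroup: in the control arm alone (n = 38), |r| = 0.30 has p = 0.067. Nothing says the correlations are run there; the one analysis that section 2.7 places in the control arm is test–retest reliability.

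**Conclusion.** The asymmetry holds as a minor fault of specification. Section 2.7 corrects Pearson correlations and leaves Spearman correlations at 0.05 each, so the multiplicity correction depends on a normality result.

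If all pairs go to Spearman, the family-wise error is between about 10% (ten pairs, two true nulls) and 66% (21 pairs, all null), with 40% for ten pairs under the complete null. It is about 5% when corrected. If only some pairs go to Spearman, fewer tests are uncorrected.

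It would go too far to infer that the trial's main findings are exposed. The correlations appear in no objective or hypothesis (section 1.2) and in no expected result (section 4), and the efficacy comparison does not use them.

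**What to change.** In section 2.7, apply the same Bonferroni correction to Pearson and Spearman correlations. The divisor should be the number of correlations in the whole family, counted across both methods: 0.005 per test for 10 pairs, 0.00238 for 21. It should not be the 0.01 that belongs to the five primary outcomes. Stating the number of correlations fixes the divisor. Alternatively, label all correlations exploratory and draw no significance claims from them.

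The 0.30 highlight can stay as a descriptive convention.

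The cost is one or two sentences. The downside is that fewer correlations will be flagged as significant. Sample size, data collection and the efficacy analysis are unaffected.

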## 3. Procedure

The study procedure intervention delivery, and data collection processes across the 12-week trial. All detailed facilitator guidelines, environmental specifications, and data management protocols are documented in Supplementary Files S2 [27]. This section provides a procedural overview; complete procedural specifications appear in Supplementary Materials (Figure 1). Data collection will begin in early January 2026 and conclude in early April 2026. Participant recruitment will be completed by 10 January 2026.

Figure 1 presents the complete study workflow across the 12-week trial. It illustrates participant flow from recruitment and baseline assessment (T0) through randomization (2:1 intervention:control), the three-phase intervention structure, mid-point qualitative assessment (T1, Week 8), post-intervention assessments (T2, Week 12), and final mixed-methods analysis combining quantitative and qualitative outcomes.

### 3.1. Intervention Delivery and Safety Monitoring

Intervention sessions are delivered weekly by trained facilitators holding CPR/First Aid certification and formal mindfulness training (qualifications detailed in Supplementary File S2 [27]). Facilitators maintain standardized session structure per Section 2.6 and detailed protocols in Supplementary File S1 (Intervention Manual) [27]. Attendance and adverse events are documented on standardized checklists completed immediately post-session.

If a participant reports severe psychological distress or adverse effects during a session, the facilitator pauses the activity, provides immediate support in a private setting, and offers clinical referral if indicated. Participation may be suspended pending further evaluation. All safety incidents are documented on incident forms and reported to the principal investigator within 24 h. If a participant reports acute psychiatric symptoms requiring hospitalization, crisis stabilization, or active suicidality, the study is suspended for that individual with clinical referral provided to a local mental health resource.

Intervention fidelity is monitored through: (1) Standardized session checklists documenting component completion, duration, deviations, and engagement level (completed immediately post-session by facilitator); (2) facilitator reflection journals documenting session flow, group atmosphere, facilitator reflections, adaptations, and concerns (reviewed weekly by Principle Investigator-PI); (3) audio recording of approximately 5–10% of sessions (stratified across phases and facilitators) for independent fidelity assessment using structured fidelity observation sheets (detailed in Supplementary File S4 [27]); and (4) monthly facilitator supervision meetings (2 h per month minimum) reviewing fidelity data, addressing participant safety, discussing facilitator well-being, and documenting protocol adaptations. Fidelity assessment occurs at three time points per site (Week 2, Week 6, Week 10) to capture early, mid-course, and late-stage implementation quality.

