## 2. Experimental Design

### 2.1. Trial Design

This study has been prospectively registered on ClinicalTrials.gov (NCT07262177; brief title: Dance-Mindfulness Intervention for Well-Being in Recreational Adults-DanceMind) and approved by the institutional Research Ethics Committee (IEC, DPESS, UTH 4-2/2.4.2025; Supplementary File S8 [27]). The protocol follows SPIRIT [28,29], TIDieR [30], and CONSORT standards [31].

This is a two-parallel group randomized controlled trial (RCT). The intervention group receives a 12-week integrated dance-mindfulness protocol grounded in polyvagal theory, motor learning science, and embodied phenomenology. The control group continues regular recreational dance activities without mindfulness or somatic-reflective components. Participants are randomly allocated 2:1 (intervention: control) using computer-generated randomization with allocation concealment.

Quantitative assessments occur at baseline (T0) and post-intervention (T2 Week 12). Qualitative data collection occurs at mid-intervention (T1 Week 8) and post-intervention (T2 Week 12). This mixed-methods design permits concurrent testing of quantitative psychological outcomes (life satisfaction, subjective happiness, psychological distress, mindful attention, leisure involvement) and qualitative embodied experiences (somatic awareness, nervous system resilience, technical confidence, creative expression, relational belonging, meaning-making).

All procedures follow ethical principles outlined in the Declaration of Helsinki. Written informed consent is obtained prior to enrollment. Participants have the right to withdraw at any time without consequence. Personal data are stored securely in encrypted databases. Each participant receives a unique study code; identifying information is separated from research data. All facilitators hold CPR/First Aid certification and mindfulness training. Session checklists document adverse events. If a participant reports intense psychological distress, the study is suspended for that individual with clinical referral provided. Facilitators are trained to recognize signs of emotional dysregulation and provide immediate basic containment (quiet space, grounding breath), without attempting psychological exploration. Control group participants receive delayed access to the intervention after post-intervention assessment (Supplementary Files S1–S8 [27]).

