### 2.6. Intervention and Control Conditions

The intervention group will consist of participants who attend 12 weekly sessions (90–100 min each) structured across three phases: (1) Foundations (Weeks 1–4), (2) Embodied Exploration (Weeks 5–8), and (3) Expressive Integration (Weeks 9–12). Each session integrates eight standardized components (warm-up/breath grounding, technical dance work, conditioning, mindful break, rhythm/improvisation, choreographed sequences, cool-down/reflective integration, phenomenological journaling). Detailed component descriptions, facilitator language, and session structure are specified in Supplementary File S1 [27].

The control group will consist of participants who continue usual recreational dance activities (preferred modern dance and/or contemporary classes) for 12 weeks, excluding mind–body practices (e.g., yoga, Pilates, tai-chi) that share overlap with the intervention. Control participants do not receive mindfulness training, somatic cuing, or reflective journaling prompts. After post-intervention assessment (T2, Week 12), control participants are offered access to the full 12–week Dance-Mindfulness program at no cost (delayed intervention, ethical equity control).

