### 3.5. Intervention Facilitator Qualifications and Training

Intervention sessions are delivered by certified modern dance educators meeting the following minimum qualifications: (1) bachelor’s degree or equivalent certification in dance or somatic movement; (2) minimum two years prior teaching experience with recreational adult populations; (3) formal training in mindfulness-based practices (MBSR certification, 200 h yoga teacher training, or safety-aware somatic training). Trauma-informed training is optional for facilitators with relevant background but not required, as the protocol maintains clear pedagogical boundaries; and (4) current CPR/First Aid certification. Prior to participant contact, each facilitator completes a 12 h standardized training module based on the Intervention Protocol Manual (Supplementary S1 [27]) and participates in 1–2 mock teaching sessions observed by the principal investigator, with written feedback incorporated before first participant session delivery.

Prior to each session, facilitators complete environmental standardization checklists documenting: studio temperature (17–22 °C), illumination (300–500 lux, LED flicker-free), acoustic baseline (≤50 dB), floor conditions (sprung or semi-sprung surface), room dimensions and participant spacing (3.5–4.0 m^2^ per participant), and confirmation of clear emergency exit pathways and visible first aid kit location (detailed specifications in Supplementary File S2 [27]).

Session attendance is recorded by the facilitator at each weekly session. If a participant misses a session, the site coordinator contacts them within 48 h to understand reasons and reschedule a make-up session if feasible, preferably within the same phase. Participants missing more than two consecutive sessions receive additional follow-up contact to assess barriers and provide support (childcare resources, transportation assistance, schedule accommodation).

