Facilitators complete standardized fidelity checklists immediately post-session documenting: completion of all eight components, actual duration of each component, deviations from protocol with justification, participant engagement level, and any adverse events or clinical concerns. Facilitators also maintain a reflective journal after each session documenting session flow, participant engagement, emotional atmosphere, personal reflections on facilitation quality, adaptations made, and any participant concerns. Reflection journals are reviewed weekly during supervision.

Facilitators meet with a designated supervisor (principal investigator or designated research staff) for weekly 1 h supervision sessions (or biweekly if multiple facilitators). Supervision includes fidelity review, problem-solving regarding participant responses or challenges, discussion of participant safety concerns, facilitator well-being and support needs, and any protocol adaptations with documented justification.

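### Adverse events are recorded on a post-session checklist with no scheduled question about the time between sessions, so harms that arise at home or end attendance are likely to be under-counted

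*Protocol article*

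**What the plan says.** The protocol article describes the routine instrument in three places. Section 2.1 (Trial Design) says: "Session checklists document adverse events". Section 3.1 (Intervention Delivery and Safety Monitoring) fixes the timing: "Attendance and adverse events are documented on standardized checklists completed immediately post-session". Section 3.5 (Intervention Facilitator Qualifications and Training) has the facilitator complete the form and lists among its contents "participant engagement level, and any adverse events or clinical concerns".

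A second, event-triggered record is given in Section 3.1: "All safety incidents are documented on incident forms and reported to the principal investigator within 24 h".

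For absentees, Section 3.5 provides that after a missed session "the site coordinator contacts them within 48 h to understand reasons and reschedule a make-up session if feasible", with further contact after more than two absences in a row. Section 2.4 promises a participant flowchart that shows attrition by group and reason.

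At Week 12 (T2), Section 3.7 has both groups complete the same five outcome questionnaires as at baseline. After that, Section 2.6 says "control participants are offered access to the full 12–week Dance-Mindfulness program at no cost".

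**The concern.** The programme combines dance technique, conditioning work and body-focused reflection. A strain or a spell of distress need not show itself while the class is running. If it appears at home, the plan has no point at which someone asks about it, so the record depends on the participant returning and volunteering it to the facilitator.

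People who stop attending because of such an event are the least likely to do that. Their reason may well be heard by the site coordinator, but the coordinator does not complete the checklist, and the contact is described as serving attendance. Events that end participation would then be the ones most likely to be absent from the harms count, and the programme would look better tolerated than it is. That matters because the Discussion presents the programme as scalable and suitable for community settings.

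**Working it through.** The article states no figure on this point, so there is none to reproduce. The check is to list each route by which a harm could come to light in someone receiving the programme, and to ask whether it includes a scheduled question about harms and whether it is stated to feed the adverse-event record.

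| Route (section) | Who is reached | Scheduled question about harms since last contact? | Stated to feed the adverse-event record? |
|---|---|---|---|
| Facilitator checklist (2.1, 3.1, 3.5) | Those the facilitator sees or hears about | No | It is the record |
| Incident form (3.1) | Anyone whose incident is noticed | No; triggered by the incident | Yes, with a 24 h report |
| 48 h absence contact, and later contact after repeated absence (3.5) | Those who miss sessions | Asks for reasons and barriers | Not stated |
| Reason for withdrawal (2.4) | Those who leave | Reason only | Goes to the flowchart; no link stated |
| T2 battery (3.7) | All randomised participants | No; five questionnaires only | Not stated |
| Interviews, Weeks 8 and 12 (2.5, 3.2) | About 30 intervention participants | Covers perceived changes and safety | Qualitative analysis; no link stated |
| Weekly journals (2.5, 3.2) | Those attending | Prompts on mood, daily life and change | A purposive sample is analysed for themes; no link stated |
| Facilitator journals and supervision (3.1, 3.5) | Those the facilitator knows about | No; records concerns already known | Not stated |

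Three cases follow from the table.

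1. **Event during a session.** The facilitator is present, completes the checklist straight afterwards, and has the incident form. Capture is good.
2. **Event at home, participant returns.** Nothing bars the facilitator from entering it, since the checklist covers any adverse event. Entry depends on the participant raising it unprompted.
3. **Event at home, participant stays away.** The coordinator's contact may obtain the reason, and a withdrawal reason may be logged. Whether either becomes a counted adverse event is left open. If the person attends T2, the DASS-21 measures depression, anxiety and stress as scores, but no item on the form asks about an injury or an adverse event.

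Two numbers give the scale of who is concerned. The planned intervention arm is 76 (Section 2.4). The interviews reach about 30 of them: 30/76 = 39%, leaving about 76 − 30 = 46 without an interview. The interview, the one scheduled contact that explicitly covers safety, therefore misses most of the arm.

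**The case against.** The strongest defence is that the article fixes when a form is filled in, not which events count. The checklist covers any adverse event, the incident form covers all safety incidents, and neither is limited to events that begin in the studio. This stands. A reader might infer that recording closes when each session ends; the text does not say so.

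A reader might also infer that dropout caused by harm goes unrecorded. The article contradicts this: reasons are sought within 48 h of an absence, and withdrawals are reported by reason and group. What remains is narrower: the article does not say that these reasons reach the adverse-event record. Nor is an early leaver without any further observation, because the absence contacts continue and T2 is planned for everyone randomised.

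Section 3 says "Data collection will begin in early January 2026 and conclude in early April 2026", and the Discussion notes that no assessment follows Week 12. From these a reader might conclude that adverse-event recording stops altogether at Week 12. That is an inference from dates for data collection and outcome follow-up; no end date for safety recording is given. Likewise, silence on monitoring or re-screening before the controls' delayed programme is missing detail, not a decision to do without them.

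Finally, Section 3 calls itself an overview and refers to supplementary files that are not shown, and these may say more. This limits the point but does not remove it, because the article itself states the instrument, its timing and who completes it.

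**Conclusion.** The point holds as a weakness in how harms are collected among programme participants. Followed as written, the plan relies on volunteered reports for anything that arises between sessions and leaves unlinked the information it already gathers on absence and withdrawal. Under-counting is likely, and most likely for events that lead people to stop attending.

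Its size cannot be given. The article states no expected event rate, no split between in-session and later onset, and no expected dropout for harm. The share of the week spent in class is not a substitute, since risk is not spread evenly over the week. A zero-event confidence bound would not help either: it describes precision, not bias.

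The conclusion assumes that the supplementary files do not already contain a between-session question or a rule linking absence reasons to the incident form. It concerns only people receiving the programme and does not touch the efficacy comparison.

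The delayed programme is a secondary matter. Up to 38 controls may take it up, and the article describes no safety recording for it. That exposure comes after the final assessment, so the gap is one of safety oversight and biases no randomised comparison.

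**What to change.** 1. At the start of each session, ask every participant one fixed question: any injury, illness or distress since the last session? Record the answer on the existing checklist.
2. In the 48 h absence contact, the later contact and at withdrawal, code the reason given. Enter any injury or distress on the existing incident form, with its existing 24 h report.
3. Put the same question on the T2 form, after the five questionnaires. Word it neutrally on timing, without mention of sessions, so that both groups can receive the same form and it does not reveal allocation to the blinded assessor.
4. State in Section 2.6 or 3.1 that the same checklists and incident forms continue in the controls' delayed programme.

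The cost is one added question on forms already in use, one code on contacts already made, and continued use of the checklists for the further 12 weeks of the delayed programme. The downside is a somewhat higher reported event count, so the report should say that events were actively asked for. No outcome measure, sample size or efficacy analysis changes.
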